## DERIVED ADHERENCE MEASURES

- From patient-reported assessment:
  - Percentage of doses taken/prescribed
  - Percentage of days of complete adherence to trial regimen
  - Percentage at VAS
- From pill count:
  - Percentage of pills returned/delivered

## Sample size of the adherence study:

all patients

## APPENDIX 14: PHARMACOECONOMICS STUDY

### SUB-STUDY TITLE

Pharmacoeconomics in HIV-infected people

### DOCUMENT VERSION AND DATE

V2.0, March 1, 2010

### RATIONALE

The introduction of HAART has resulted in significantly higher costs for therapeutics, while reductions have been observed in healthcare resource use due to the prevention of opportunistic infections (Gebo et al, 1999). Since the mid-1990s, this has resulted in a shift from inpatient towards outpatient care (Tramarin et al, 2004, Hubben et al, 2008). Given the fact that HIV prevalence rates are increasing due to falling death rates (for instance more than 56000 prevalent cases were estimated in Italy at the end of 2005 – Suligoi et al, 2006), the impact of HIV on national health budgets can be expected to increase (UNAIDS, 2007; Yazdanpanah et al., 2002).

According to an Italian recent study, the societal cost (direct, indirect, intangible) of HIV/AIDS (Hubben et al, 2008), is substantial, related to the treatment regimen followed, to the HAART success or failure, highly influenced by the indirect costs (loss of productivity).

The two alternative treatment strategies of the trial are compared in terms of cost-consequence: specifically the difference in the relevant costs and effects (see below for details), between the comparative options, are computed. The following possible scenarios may be identified:

1. The new/innovative option is both more effective and more costly than the reference option. In this case, the ratio of the difference of costs with the difference of effects is computed to estimate the Incremental Cost Effectiveness Ratio (ICER), i.e. the amount of incremental costs necessary to gain one unit of effects, for the more effective treatment option.
2. The new/innovative option is more effective and also less costly. In this case this treatment option is recognised to be dominant, as contemporarily more effective and less costly

### OBJECTIVE

- To compare the two different regimens in terms of: 1) cost-effectiveness and 2) cost-utility in a subset of patients (Italy)
- To describe in-patient care resource utilisation in all patients

### ENDPOINTS

- cost-effectiveness
- cost-utility

#### **SUB-STUDY COMPONENTS AND PROCEDURES**

- Data regarding in-patient care resource utilisation is recorded in all patients from W00 on.
- A detailed pharmacoeconomics substudy is conducted in Italy only:
- For patients participating in the trial in Italy, economic data are collected at W00, W24, W48, W64 and W96.
- Perspective of the analysis: the perspective of the main payer(s) is adopted (National Health Service or other third party payers or patients; country specific issue). Costs and effects to be included in the analyses: both direct costs (for instance for drug therapy, for hospitalisation) and effects (expressed in clinical terms, as from the main study) and intangible costs and effects (i.e. impairment/improvements of HRQoL) are analysed.
- Technique: Cost-Effectiveness and Cost-Utility Analysis is conducted in order to estimate the incremental cost per physical/clinical effectiveness and/or per Quality Adjusted Life Years (QALY) gained. To estimate the QALY the utility is estimated from the health states reported with the EQ-5D and the social tariffs estimated and approved within the EuroQoL group.
- Time horizon: the time horizon adopted for this study is the same as for the core trial: accordingly costs and effects occurring after the first year of observation are discounted.
- Effects on health related quality of life, expressed in terms of utility, obtained from the assessment with the EQ-5D questionnaire (quality of life assessment) are also evaluated.

## APPENDIX 15: VIRAL AND IMMUNOLOGIC DYNAMICS AND INFLAMMATION SUB-STUDY

### TITLE

Viral and immunologic dynamics and inflammation

### DOCUMENT VERSION AND DATE

V4.0, November 19, 2010

### RATIONALE

Apoptotic loss of uninfected T cells appears to be a consequence of the generalised chronic high levels of immune activation that accompany pathogenic HIV infection. This concept is supported by observations that T cell activation is a good predictor of disease progression in untreated HIV-infected individuals, and that CD4 T cell depletion correlates more closely with levels of immune activation than with viral load. Thus, immune activation is considered to be a major factor contributing to HIV-related quantitative and functional immune deficiencies and CD4 defects as well as to HIV-related cardiovascular alterations. It is supposed to be linked to HIV both directly through activation of immune competent cells releasing pro-inflammatory cytokines or adhesion molecules and indirectly through tissue (mainly gut) associated damages.

Some cellular markers of activation such as CD38 and HLA-DR on CD8 T cells have been clearly defined as the best markers of immune activation. The T cell immune activation is also detectable on CD4 T cells and is known to favour HIV entry and integration partly by enhancing cell surface expression of CCR5, the main HIV entry co-receptor, in parallel to HLA-DR. In both cases the classical monitoring using the enumeration of percentages of CD4 or CD8 T cells expressing those markers can be improved by using a direct quantification of the CD38 or CCR5 molecules, thus allowing a highly sensitive measurement of immune activation and its consequences for HIV entry.

Many seric markers of immune activation have also been proposed such as pro-inflammatory cytokines released by the activated immune competent cells, among which IL-6 appears as the best marker, or adhesion molecules shed from the endothelial surface, among which V-CAM appears as the best marker.

NEAT-001/ANRS 143 is a 2 year randomised open-label, multinational, multicentre trial in HIV-infected naïve patients comparing two regimens of antiretroviral therapy including a combination of 2 potent new ARV drugs (boosted-darunavir + raltegravir) and a darunavir/ritonavir containing triple therapy (darunavir/r + tenofovir/emtricitabine). The new raltegravir containing drug combination is supposed to induce a very rapid, profound and sustained reduction in viral load. However, these observations require confirmation. Furthermore, the mechanism of such a reduction in potency requires study. For instance, it remains unclear whether any increased potency defined as more rapid decline of viral load is reflected in a reduction in the circulating reservoir, or the intracellular state of the viral genome. These parameters can be determined by quantifying episomal versus integrated proviral DNA, and also studying the nature of viral mRNA produced through transcription. Increased potency of the drug regimen would also be accompanied by a reduction in immune activation and a rapid, potent and sustained immune restoration. This supposed profound reduction in immune activation requires highly sensitive and reliable methods of

monitoring immune activation. Furthermore immune activation, endothelial damage, vascular dysfunction, activity of proinflammatory cytokines, hypercoagulable state and dyslipidemia are different mechanisms that could increase HIV-related cardiovascular risks. Therefore it is still an open scientific question if different types of antiretrovirals are associated with different metabolic and/or proinflammatory changes that could impact in different ways on the cardiovascular risk of HIV-infected patients. The NEAT 001/ANRS 143 trial thus provides a unique opportunity to evaluate within the network of high tech immunology laboratories linked to NEAT, the ability of those new drug combinations at better or more sustainably reducing immune activation than more conventional regimens using highly sensitive markers of immune activation and therefore at allowing a better efficacy and tolerability of these drug regimens.

## OBJECTIVES

To study the correlation between viral decay and immunologic parameters

To compare between the two treatment strategies:

- the early immunologic dynamics in relationship with the viral dynamics
- the efficacy to
  - reduce the immune activation over 96 weeks as assessed by the numbers of CD38 molecules expressed by CD8 T cells and their co-expression with HLA-DR on CD8 T cells
  - reduce the CD4 cell expression of CCR5, the main HIV co-receptor of entry, the expression of which is associated to immune activation as assessed by the quantification of CCR5 molecules on CD4 T cells and their co-expression with HLA-DR
  - reduce plasma levels of seric markers of immune activation linked to inflammation and cardiovascular alterations (among those: IL-6, V-CAM...)
  - induce immune restoration of naïve and memory T cells numbers and functional competence against pathogens and HIV
- lipid changes
- glucose metabolism changes
- endothelial damage
- change in cardiovascular risk
- change in proinflammatory cytokines
- change in coagulation parameters

To identify the best surrogate of viral suppression in the two treatment arms

To study the association between residual viral replication, proviral DNA, immune activation, endothelial activation, and inflammation

## ELIGIBILITY CRITERIA

### Inclusion Criteria

- Patients having signed the consent form for the NEAT 001/ANRS 143 trial and having been successfully screened for the trial
- Patients followed in a centre participating in the Viral and immunologic dynamics and inflammation sub-study
- Signed consent for the sub-study

### Non-inclusion Criteria

- Hemoglobin  $\leq$  10 g/dl (assessed during the last 3 months prior to screening visit)

If hemoglobin level falls  $\leq 10$  g/dl between W00 and W02, sampling for this sub-study should be suspended until hemoglobin is  $> 10$  g/dl.

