### 7.2 Screening visit (W-6 to W-1)

A screening assessment for eligibility is performed between week -6 and week -1.

If patients with acute opportunistic infections are screened, the screening period should not exceed 2 weeks (screening visit between week -2 and week -1).

Signed and written informed consent for the trial must be obtained at latest at the screening visit and prior to the initiation of any study related intervention.

Screening procedures include:

- demographic information: date of birth, sex, ethnic group, country of birth
- history of HIV-associated conditions: mode of infection, CD4 nadir, date of first positive HIV-1 test, date of last HIV-1 negative test (if known), CDC stage
- documentation of historical genotype testing results, if available
- relevant medical history
- current medical conditions
- current medication
- recording of contraceptive methods in women
- assessment of inclusion and non-inclusion criteria
- complete physical examination including height and body weight (nude or light clothing only), heart rate and blood pressure
- blood sample for local laboratory assessments

laboratory assessments:

- plasma HIV-1 RNA
- HIV-1 genotypic resistance profile (if not previously available. Original test results of previous genotypic resistance profile must be available)
- HIV-1 subtype (if not previously available)
- CD4+ (mandatory even if  $CD4 \leq 500/mm^3$  on a sample taken within 3 months before screening)
- hepatitis serology: HBs Ag; HCV antibodies (if not previously available or if last assessment > 12 months before screening and HCV Ab negative, HBs Ab and HBc Ab negative)
- haematology: complete blood count, platelets; clinical chemistry: creatinine, alkaline phosphatase, ALAT, ASAT, albumin
- coagulation: prothrombin time (INR)
- pregnancy test (serum beta-HCG) in all women of child bearing potential
- estimation of glomerular filtration rate (see Cockcroft & Gault equation in appendix 7)

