### 7.5.2 Visit W04

Visit W04 is performed between 26 and 30 days after the baseline visit.

Patients should not take their trial drugs on the morning of the day of the visit (due to drug concentration assessment at W04; drug intake must be at least 5 hours prior to blood draw).

Procedures at visit W04 include:

- medical history and adverse events since the last visit
- medication history since the last visit
- recording of contraceptive methods in women
- recording of in-patient care resource utilisation (type and duration of hospital stays)
- complete physical examination (when clinically indicated), blood pressure and heart rate + morphologic evaluation, including measurement of weight, hip and waist circumference
- self-completed patients' reported outcomes questionnaire (quality of life, adherence)
- blood sample for local laboratory assessments (recording of time and date of intake of the last meal, of last drug intake and of blood draw)

laboratory assessments:

- plasma HIV-1 RNA
- CD4+ T-cells
- haematology: complete blood count, platelets
- clinical chemistry (patient has to be fasting for at least 10 hours prior to blood draw):  
creatinine, sodium, potassium, phosphate, calcium, total and indirect bilirubin,  
alkaline phosphatase, GGT, ALAT, ASAT, lipase, CK, urea, albumin, bicarbonate, uric  
acid, triglycerides, cholesterol (total, HDL, LDL)
- blood samples for biobank: 3 EDTA vials (7 ml per vial)
  - preparation of 4 aliquots of 1 ml of plasma for storage
  - preparation of 4 aliquots of 1 ml full blood for storage

- blood sample for centralised drug concentration analysis: Sampling of 10 ml in EDTA vials (one 10 ml vial or two 7 ml vials) and preparation of 4 aliquots of 1 ml of plasma for storage. Handling and shipment are described in a specific SOP.)
- urine sample:
  - dipstick assessment of glucosuria, proteinuria, leukocyturia, erythrocyturia and pH
  - protein/creatinine ratio, phosphate, uric acid, glucose
  - pregnancy test (urine beta-HCG) in all women of child bearing potential
  - preparation of 4 aliquots of 1 ml urine for biobank storage
- estimation of glomerular filtration rate (see Cockcroft & Gault equation in appendix 7)
- counting of returned drugs
- study drug dispensation
- scheduling of visit W08

Patients participating in the Viral and Immunologic Dynamics and Inflammation sub-study have additional blood sampling at this visit (see appendix 15).

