| Visit                                                                                                         | W-6       | W00   | W01  | W02  | W03  | W04   | W08   | W12   | W18   | W24   | W32   | W48   | W64    | W80    | W96    |
|---------------------------------------------------------------------------------------------------------------|-----------|-------|------|------|------|-------|-------|-------|-------|-------|-------|-------|--------|--------|--------|
| Week                                                                                                          | -6 to -1  | 0     | 1    | 2    | 3    | 4     | 8     | 12    | 18    | 24    | 32    | 48    | 64     | 80     | 96     |
| Day                                                                                                           | -42 to -7 | 0     | 7±2  | 14±2 | 21±2 | 28±2  | 56±7  | 84±7  | 126±7 | 168±7 | 224±7 | 336±7 | 448±15 | 560±15 | 672±15 |
| Additional sampling in sub-study participants                                                     |           |       |      |      |      |       |       |       |       |       |       |       |        |        |        |
| Bone sub-study:
- Serum biobank                                                                            |           | 5 ml  |      |      |      |       |       |       |       |       |       | 5 ml  |        |        | 5 ml   |
| - Urine biobank                                                                                               |           | 5 ml  |      |      |      |       |       |       |       |       |       | 5 ml  |        |        | 5 ml   |
| Viral and Immunologic Dynamics and Inflammation sub-study:
- Full blood (ACD or heparin tube)  |           | 50 ml | 5 ml | 5 ml | 5 ml | 30 ml | 30 ml | 30 ml |       | 50 ml |       | 50 ml |        |        | 50 ml  |

1 Please refer to sub-study protocols for details  
2 Samples to be shipped immediately at room temperature to closest core immunology lab (see appendix 15)

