#### SUB-STUDY COMPONENTS AND PROCEDURES

The assessments evaluate in the two different treatment strategies (see table 1, page 136).

- CD4 count at W00, day 2-3, W01, W02, W04, W08, W12, W18, W24, W32, W48, W64, W80, W96
- immunologic markers W00, W01, W02, W03, W04, W08, W12, W24, W48, W96:
  - level of expression of CCR5 on CD4+ T cells in association to immune activation as assessed by the quantification of CCR5 molecules on CD4 T cells in relationship with the level of CD38 expression on CD8 T cells and the proportions of activated HLA-DR+ CD4+ and CD8 T cells, and the proportions of naïve and memory CD4 T cells
  - numbers and functional competence of T cells against pathogens and HIV
- markers of endothelial activation and inflammation at W00, W02, W04, W08, W12, W24, W48, W96 (among those: Ultra-sensitive C-reactive protein, IL-6, V-CAM, serum amyloid A, serum amyloid P etc)
- coagulation markers: D-dimer, PAI-1, prothrombin fragment 1+2 at W00, W48, W96
- intensive lipids: total cholesterol, triglycerides, HDL-cholesterol; LDL-cholesterol, apo-A1, apo-B, lipoprotein profiling by NMR spectroscopy at W00, W04, W48, W96
- intensive glucose: fasting glucose and insulin, urine glucose (dipstick), fasting proinsulin, fasting C-peptide, HOMA at W00, W04, W48, W96
- plasma HIV-1 RNA at W0, day 2-3, W01, W02, W03, W04, W08, W12, W18, W24, W32, W48, W64, W80, W96
- total proviral DNA, episomal and integrated DNA, and spliced/unspliced RNA at W00, W01, W02, W03, W04, W08, W12, W24, W48, W96
- residual viral replication (HIV-1 RNA  $< 1$  copy/ml) at W24, W48, W96

Patients participating in this sub-study undergo additional blood sampling at W00, day 2-3, W01, W02, W03, W04, W08, W12, W24, W48, and W96 (see table 2, page 137). This

includes three extra visits to the study site (day 2-3, W01, W03) in addition to the core protocol visits.

This study requires core laboratories of immunology/virology with high tech performances in flow cytometry (these core laboratories could be in France, Italy, Germany, UK, Spain) and molecular virology, and local laboratories of immunology with very good performances in viable cell cryopreservation and reliable capacities of plasma storage.

Blood samples for analysis of immunologic and virologic markers need to be sent at room temperature and arrive at the closest core immunology lab during working hours and no later than 12h after sampling (see table 2, page 137).

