| Sampling for immediate shipment to core immunology lab  | X               |         | X               | X               | X               | X               | X               | X               |     | X               |     | X               |     |     | X               |
| Total amount blood sample (ACD or heparin tubes) for centralisation | 50 mL           |         | 5 mL            | 5 mL            | 5 mL            | 30 mL           | 30 mL           | 30 mL           |     | 50 mL           |     | 50 mL           |     |     | 50 mL           |
| Temperature of shipment                                             | RT  |         | RT  | RT  | RT  | RT  | RT  | RT  |     | RT  |     | RT  |     |     | RT  |

1 Samples must arrive at the core immunology laboratory during working hours and no later than 12h after sampling.

2 RT = room temperature

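### Appendix 15 sub-study: the haemoglobin trigger for suspending research sampling closes at W02, before 80% of the sub-study's centralised blood is drawn, and the entry haemoglobin may predate screening

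*Protocol*

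**What the plan says.** The non-inclusion criteria of Appendix 15 bar patients with haemoglobin of 10 g/dl or less, the value being "assessed during the last 3 months prior to screening visit". The same paragraph governs sampling after entry: for a fall to 10 "g/dl between W00 and W02, sampling for this sub-study should be suspended until hemoglobin is" back above 10 g/dl. It gives no other trigger.

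The components section of Appendix 15 schedules "additional blood sampling at W00, day 2-3, W01, W02, W03, W04, W08, W12, W24, W48, and W96". Volumes are in Appendix 15, Table 2, in the row "Total amount blood sample (ACD or heparin tubes) for centralisation", and again in Biobank Table 2 of Appendix 8, where the W00 to W12 entries read "50 ml | 5 ml | 5 ml | 5 ml | 30 ml | 30 ml | 30 ml". Both tables then give 50 ml at W24, W48 and W96.

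The core trial measures blood counts throughout. Section 7.2 lists "haematology: complete blood count, platelets; clinical chemistry: creatinine, alkaline phosphatase, ALAT, ASAT, albumin" at screening, and Sections 7.4 and 7.5 list "haematology: complete blood count, platelets" at W00, W02, W04 and the later core visits to W96. On timing, Section 7.2 says: "A screening assessment for eligibility is performed between week -6 and week -1".

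**The concern.** The sub-study treats haemoglobin of 10 g/dl or less as a reason not to take its extra blood. A safeguard of this kind should cover the period in which the blood is taken. Here the trigger covers the first two weeks of a 96-week schedule, and most of the volume comes later. The entry check has a related weakness: it points to a value obtained before screening and does not mention the count done at screening.

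At stake is the protection of sub-study participants, some of whom may have advanced disease: the trial admits patients with acute opportunistic infection, and the monitoring committee section (13.4) aims for 20-25% with CD4 below 200/mm³. No efficacy estimate or error rate is involved.

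**Working it through.** The protocol states no cumulative volume, so there is no figure of its own to reproduce. The inputs are the per-visit volumes, which are identical in Appendix 15, Table 2 and Biobank Table 2.

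| Visit | W00 | W01 | W02 | W03 | W04 | W08 | W12 | W24 | W48 | W96 |
|---|---|---|---|---|---|---|---|---|---|---|
| ml | 50 | 5 | 5 | 5 | 30 | 30 | 30 | 50 | 50 | 50 |
| Running total | 50 | 55 | 60 | 65 | 95 | 125 | 155 | 205 | 255 | 305 |

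**Share outside the trigger window**
- Up to and including W02: 50 + 5 + 5 = 60 ml.
- After W02: 305 − 60 = 245 ml, and 245/305 = 80.3%.
- The 30 ml and 50 ml draws after W02: 3 × 30 + 3 × 50 = 240 ml, and 240/305 = 78.7%.

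**Sensitivity to what is counted**
- The local-laboratory samples at day 2-3, W01, W02 and W03 have no stated volume. Assume x ml each; only W03 falls after the window, so the share is (245 + x)/(305 + 4x). For x = 0, 5 and 10 this gives 80.3%, 76.9% and 73.9%.
- Core biobank tubes (Biobank Table 1) come to 40 tubes × 7 ml = 280 ml, of which 6 × 7 = 42 ml by W02. Including them, (245 + 238)/(305 + 280) = 483/585 = 82.6%.

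The share therefore lies between 74% and 83% under these assumptions.

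**Age of the entry haemoglobin at the W00 draw**
- Three months is about 13 weeks, and screening precedes W00 by 1 to 6 weeks.
- The oldest admissible value is thus 13 + 1 = 14 weeks with the shortest screening and 13 + 6 = 19 weeks with the longest. For acute opportunistic infection, where screening is capped at two weeks, it is 13 + 2 = 15 weeks.

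**Whether another rule fills the gap**
- The core eligibility criteria (Sections 4.2 and 4.3) set no haemoglobin limit.
- Section 7.12.4 on treatment-limiting adverse events starts at Grade 3 and concerns study drugs. On the Appendix 6 scale, Grade 3 haemoglobin is 6.5–6.99 g/dl.
- Blood counts continue at core visits after W02, but no sub-study action is attached to them.

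As an illustration, a patient who passes at W00 and W02 and has 9.0 g/dl at W08 is Grade 1, meets no suspension rule in this protocol, and is due 30 ml at W12 and 50 ml at W24.

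**The case against.** A reader might infer that anaemic patients go on giving 30 to 50 ml samples. The text does not support that. The window limits when a fall triggers suspension, not how long suspension lasts, so a patient at or below 10 g/dl by W02 misses later draws until recovery. The gap concerns a first fall after W02. Even then, the protocol shows only that no written rule stops the draw, not that the draw will happen.

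A reader might also infer that an old entry value lets low haemoglobin through unchecked. The W00 and W02 counts catch much of this: read naturally, a patient found at 9.3 g/dl at either visit is suspended. What remains is mainly the first 50 ml draw, because the W00 count is taken at the same visit.

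The pace of sampling also favours the plan. It runs at 60 ml in the first two weeks, 95 ml over the next ten, and 150 ml over the remaining 84 weeks, so 150/245 = 61% of the volume outside the window is in three widely spaced draws. Tying the check to the densest phase can be defended. The trial's scale leaves 9.5–10.0 g/dl ungraded and calls 8.0–9.4 g/dl Grade 1, and the documents give no blood-volume limit or anaemia rate from which harm could be derived.

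Finally, Section 2.7.2 describes the sub-study appendices as summaries, and Appendix 8 points to separate sub-study protocols that are not shown. They may deal with later haemoglobin values.

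All of this narrows the point. It does not explain why the sub-study's own threshold ceases to trigger anything from W03, when 30 ml draws are due at W04, W08 and W12.

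**Conclusion.** The point holds in a limited form. As written, the trigger window covers 60 of 305 ml of centralised sub-study blood and leaves 245 ml (80%) outside it. A first fall to the sub-study's threshold after W02 meets no suspension rule in this protocol. The entry value can be up to 14 to 19 weeks old at W00 although a count is done at screening; the W00 and W02 counts only partly compensate.

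The 80% refers to the centralised ACD/heparin samples, and the age range takes three months as 13 weeks. The conclusion rests on this protocol alone; the separate sub-study protocol could change it, although any difference would itself need reconciling with the explicit window here. The sub-study plans 40 patients per arm, about 80 in all. This is worth correcting for participant protection, and it does not touch the primary endpoint or its analysis.

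**What to change.** In Appendix 15, reconcile the trigger window of the haemoglobin suspension with the draw schedule through W96. State how the haemoglobin used for entry relates to the blood count done at screening and to the counts at core visits. Check both points against the separate sub-study protocol so that sites see one consistent rule. The threshold and the clinical rule are for the sponsor to set.

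The edit is one or two sentences and needs no new test at core visits. The cost is a few missing sub-study samples. There are two practical limits: no blood count is scheduled at day 2-3, W01 or W03, and at core visits the count and the research draw fall at the same visit. The revised text should say which result applies to which draw.
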